### Secondary outcomes

2.7

#### Oxygen consumption (VO_2_), carbon dioxide production (VCO_2_), and resting energy expenditure (REE)

2.7.1

Indirect calorimetry (IC) is a noninvasive method that analyzes the amount of heat generated by the whole body according to the substrate utilization. The data provided by calorimetry are resting energy expenditure (REE) that is calculated from the amount of VO_2_ and VCO_2_ through the respiratory gases. The inspired fraction of oxygen is measured through the inspiratory branch of a mechanical ventilator. The expiratory gases pass through a mixing chamber where the fraction of expired air of oxygen and carbon dioxide are analyzed.^[26]^ Patients will be submitted to IC during baseline and study protocol. The IC will be measured by a portable calorimeter DELTATRAC II Metabolic Monitor (Datex-Ohmeda, Helsinki, Finland) connected to a mechanical ventilator (Evita XL, Dräger medical, Lübeck, Germany) for 30 minutes in a stable condition without manipulation of the upper airways or changes of the ventilator parameters. The intensive care unit staff will be trained in how to proceed when the IC is running. We consider steady state to be the point after 5 consecutive minutes measurement when oxygen consumption and carbon dioxide production vary by ±10%. This technique was employed in some of our previous studies^[27–29]^ and was validated elsewhere.^[30]^ The protocol will initiate after warming the calorimeter for 30 minutes. The gas and pressure (95% O_2_/5% CO_2_) is calibrated according to the manufacturer's instructions.

### Other outcomes

2.8

#### Hemodynamic variables

2.8.1

The change in hemodynamic and respiratory variables will be measured, including heart rate, blood pressure, oxygen saturation, and breathing frequency. The change in cirtometry will be collected by the measurements of the circumference of the gastrocnemius muscle.

#### Interventions

2.8.2

The protocols will be carried out in adult intensive care center at a tertiary University Hospital.

#### Intervention protocol – decubitus position with the limbs raised and NMES

2.8.3

The patient will be positioned on a headboard at 30° in the decubitus position with the limbs raised to 20°. The location of the electrical current will be cleared with trichotomy when necessary. Adhesive electrodes 90 x 50 mm will be positioned in the gastrocnemius. The stimulator device will be the Neurodyn II (Ibramed, Sao Paulo, Brazil) to provide symmetrical biphasic pulses of 50 Hz, 250 μsec pulse duration, 2 seconds on (1 second of time of rise and 1 second of time of decay), and 5 seconds of rest during 30 minutes at an intensity capable of generating visible contractions and articular motion (Fig. 2).

**Figure 2 F2:**
[figure not shown]
Intervention protocol.

#### Control protocol – decubitus position with the limbs raised without NMES

2.8.4

The patient position will be the same used for intervention protocol (headboard to 30°, decubitus position with the limbs raised to 20° for 30 minutes.

Adverse event will be defined as any change in mean arterial blood pressure less than 65 mm Hg, heart rate <50 or >140 bpm, arrhythmias with hemodynamic consequences, myocardial ischemia, decrease in 10% of SpO_2_ baseline value, or <88% for more than one minute and pain during the NMES session. Pain will be evaluated through the Brazilian version of the Behavioural Pain Rating Scale^[31]^ to measure pain in unconscious patients under mechanical ventilation and unable to communicate verbally. If any adverse event happen, the session will be interrupted and the event will be related.

This study is a trial with a short duration and with known minimal risks; therefore, data-monitoring committee is not necessary.

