In addition, it is common to use sedation and mechanical ventilation in septic shock patients. The frequent use of sedation limits mobilization of critically ill patients usually showing a progressive loss of muscle strength and functionality. Physiotherapy can use different techniques to help these patients increase muscle strength, recovery of functional status, decrease the length of weaning of mechanical ventilation, and decrease the duration of delirium.^[10,11]^ One of these techniques used to recruit muscles in the intensive care environment is neuromuscular electrical stimulation (NMES). The NMES is directed to those patients who cannot cooperate with physiotherapy due to sedation or decreased muscle strength, and it allows the patients to perform exercises in passive, assisted, and active modes.^[12]^ This noninvasive therapy is applied regardless of the patient's effort and produces a muscle contraction in response to a externally generated low-voltage electric impulse, which is conducted through electrodes placed on the skin over the muscle group to be stimulated.^[12,13]^

Some studies have shown evidence that the electrical stimulation reduces muscle atrophy and the time of weaning from mechanical ventilation and therefore increases muscle strength in critically ill people^[14–16]^; beneficial results of NMES have been demonstrated in patients with sepsis. In these patients, Rodriguez et al^[17]^ showed improved muscle strength—especially those in critical condition. Stefanou et al^[18]^ demonstrated an increase in EPCs after NMES. In patients with septic shock, only 1 study has evaluated the effects of NMES^[19]^; it demonstrated a marked decrease in the quadriceps volume independently of the use of NMES. However, the benefits of NMES are not limited only to the maintenance of muscle strength.^[14,15]^ Literature findings suggest that there is a potential benefit of NMES in acute activation of microcirculation observed by the increased rate of oxygen consumption and reperfusion as measured by infrared spectroscopy.^[20,21]^

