### Study participants and eligibility criteria

2.2

The patients admitted to the intensive care unit are eligible if they present in the first 72 hours after the diagnosis of septic shock according to the international consensus definition of septic shock. They should have stable hemodynamic through fluid resuscitation, vasoactive drugs, and mechanical ventilation as described above.

Exclusion criteria will include patients aged 18 years or less or over 65 years, pregnant women, brain death, neuromuscular diseases, or the use of a pre-existing neuromuscular blocker in the last 24 hours.

Contraindications for the use of NMES will include fractures, burns, skin lesions, systemic vascular impairment diseases such as systemic lupus erythematosus, thromboembolic disease, deep vein thrombosis (which was not therapeutically anticoagulated for more than 36 hours), lower limb amputations, cardiac pacemaker, thrombocytopenia less than 20,000/mm^3^, body mass index greater than 35 kg/m^2^, important lower extremity edema, agitation, and/or signs of pain during the electrical stimulation.

Contraindications to begin or continue NMES procedure will include the following: mean arterial blood pressure less than 65 mm Hg, use of vasopressor >50% of the maximum dose (dopamine >12.5 μg/kg per minute; vasopressin >0.02 U/min and norepinephrine >1 μg/kg per minute), heart rate <50 or >140 bpm, arrhythmias with hemodynamic consequences, myocardial ischemia, temperature <34^ o^C or >39^o^C, intracranial pressure >20 cmH_2_O, decrease in 10% peripheral oxygen saturation (SpO_2_) baseline value or <88% for more than 1 minute.

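### The adverse event definition in section 2.8.4 is a closed list with no catch-all and no post-session window, counts pain only under NMES, and does not match the start-or-continue criteria in section 2.2

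*Protocol article*

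**What the plan says.** The definition stands in section 2.8.4, under the control protocol. It opens with "Adverse event will be defined as any change in mean arterial blood pressure less than 65 mm Hg", adds heart rate below 50 or above 140 bpm, goes on to "arrhythmias with hemodynamic consequences, myocardial ischemia, decrease in 10% of SpO_2_ baseline value", and closes with "<88% for more than one minute and pain during the NMES session". The consequence follows: "If any adverse event happen, the session will be interrupted and the event will be related". The section ends by dispensing with a monitoring committee: "This study is a trial with a short duration and with known minimal risks; therefore, data-monitoring committee is not necessary".

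Section 2.2 has two related lists. The first gives conditions that bar NMES, among them "fractures, burns, skin lesions, systemic vascular impairment diseases such as systemic lupus erythematosus, thromboembolic disease, deep vein thrombosis", together with low platelets, agitation and signs of pain under stimulation. The second gives limits for starting or continuing a session. It covers pressure, heart rate, arrhythmia, ischemia and saturation, and also vasopressor dose, temperature and intracranial pressure.

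Section 2.5 sets a wash-out of 4 to 6 hours between the two protocols and a second phase three days after the first assessment. The hypothesis at the end of the Introduction and the last paragraph of the Discussion put the safety question as whether NMES can be given without metabolic or hemodynamic harm.

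**The concern.** A list of limits that tells staff when to stop a session serves a different purpose from a definition of what counts as harm. Section 2.8.4 uses one list for both. Whatever is not on it does not enter the safety results, however clearly it follows from the stimulation. That is a stated rule, not a detail left out of a condensed article: wider wording in a fuller protocol would contradict it.

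The safety conclusion is at stake. If the trial reports few or no adverse events, a reader will take that as evidence about NMES in septic shock, when part of it would come from how the term was defined. The mismatch with section 2.2 matters most, because it falls inside the hemodynamic question that the trial says it will answer.

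**Working it through.** No figure in the protocol depends on this definition, so the check is mainly a comparison of text.

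**Step 1: is the list closed?** It is introduced as what an adverse event will be defined as. It has no wording such as including, and no item for any other untoward event. It is closed.

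**Step 2: what window does it carry?** None is stated. The words on the NMES session come directly after pain, and there are two readings.
- They qualify pain alone. Pain is then the only item that cannot be counted under control; the other items apply to both protocols.
- They qualify the whole list. No event in a control session would then count, and no item could be compared.

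The first reading is the more natural, and pain is lost to comparison under both. The action sentence presupposes a running session, so it says nothing about the wash-out or the days before phase two.

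**Step 3: set the lists side by side.**

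| Item | Section 2.2 | Adverse event in 2.8.4 |
|---|---|---|
| Mean arterial pressure below 65 mm Hg | start/continue limit | yes |
| Heart rate below 50 or above 140 bpm | start/continue limit | yes |
| Arrhythmia, myocardial ischemia | start/continue limit | yes |
| Saturation limits | start/continue limit | yes |
| Vasopressor above half the maximum dose | start/continue limit | no |
| Temperature below 34 or above 39 °C | start/continue limit | no |
| Intracranial pressure above 20 cmH2O | start/continue limit | no |
| Signs of pain | contraindication | NMES session only |
| Agitation | contraindication | no |
| Skin lesion, burn, thrombosis, thromboembolic disease | contraindication | no |

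**Step 4: follow three cases through the text.**
- Vasopressor dose rises past the section 2.2 limit while mean pressure stays at 65 mm Hg or above. NMES may not continue, yet no listed criterion is met. The hemodynamic variables named in section 2.8.1 do not mention vasopressor dose either.
- A skin lesion is seen when the electrodes come off, with no pain score recorded. No listed criterion is met.
- An unlisted event, such as bleeding without a fall in pressure, occurs in the wash-out or before phase two. No listed criterion is met.

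**Step 5: size, as an illustration only.** The documents give no event rates. Assume that all 31 patients receive NMES and that a fraction p has an unlisted event with no listed sign. The chance that at least one patient has it is 1 − (1 − p)^31:
- p = 1%: 1 − 0.99^31 = 0.27
- p = 5%: 1 − 0.95^31 = 0.80
- p = 10%: 1 − 0.90^31 = 0.96

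Under the closed list the recorded count is zero in each case. With full recording, 0 of 31 would give a one-sided 95% upper bound of 1 − 0.05^(1/31) = 9.2%. With the closed list, a zero for such an event gives no bound at all.

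**The case against.** The strongest defence has three parts. First, this is a condensed article, and categories of serious events, follow-up windows and reporting routes are commonly left to the full protocol. That stands for those details, and their absence is not the point here. It does not rescue a definition that the article states in closed form. Second, the safety question is limited to metabolic and hemodynamic effects, and the list fits that. This holds in part, but the missing vasopressor limit lies inside that question. Third, wider recording adds little comparison with a 4 to 6 hour wash-out. This is true of late events. It is not true between the first and second sessions of phase one, when each randomized group has received only one protocol.

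A reader might infer more than the documents support:
- *The list holds only vital signs and pain.* It also names arrhythmia and myocardial ischemia.
- *Collection legally ends with the session.* That is inferred. No window is stated, and the action sentence is not a collection rule.
- *The protocol itself names skin and thromboembolic harm as risks of NMES.* Section 2.2 gives them as contraindications, beside items such as amputation and pacemaker that cannot be harms of stimulation.
- *Such events can never be counted.* An embolic event with desaturation or hypotension could meet a listed criterion.
- *A patient with a new lesion would be stimulated again unchecked.* Section 2.2 would already bar NMES in a patient with a skin lesion or thromboembolic disease.
- *Only a small percentage of trial time is covered.* Such a figure rests on the inferred window and on a schedule in a figure not shown, and it measures clock time, not missed events.
- *The minimal-risk statement contradicts the Introduction, which says "In patients with septic shock, only 1 study has evaluated the effects of NMES".* It does not: the article also cites NMES studies in sepsis and in critically ill patients.

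**Conclusion.** The point holds as a defect of definition. The list is closed, has no stated post-session window, excludes skin injury and other unlisted events, and counts pain under one protocol only. It also leaves out three limits that section 2.2 uses to withhold or stop NMES. The direction of the error is known: harm is undercounted. The amount is not known, because no event rates are given, and the range in the working rests on assumed risks. The primary endothelial progenitor cell analysis is not touched; the safety conclusion is. The change should be made, but it does not put the trial's main result in doubt. The verdict rests on a literal reading of section 2.8.4. If the full protocol already defines adverse events openly, the article and that protocol need to be brought into line.

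**What to change.** In section 2.8.4, separate two things that are now one.

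1. **Session-interruption criteria.** Give these as their own list and reconcile them with the start-or-continue list in section 2.2. Which limits apply, and what is required before a patient's next session, are clinical rules for the sponsor to settle. The two sections need only agree. Record every interruption with its reason, so that a stop for any criterion reaches the results.
2. **Adverse event definition.** Define it as any untoward event, under either protocol, from the start of the first session to a stated time after the last. Include the skin under the electrodes at removal, and thromboembolic or bleeding events from the intensive care chart. Assess pain in the same way in the NMES and control sessions. Record onset time and the last protocol received.

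Report events by last protocol received. Events before the second session of phase one can be compared between the randomized groups. State that later events cannot be attributed once both protocols have been given.

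The cost is a chart check and a skin look by the team that already attends the sessions. The downside is a longer list of background events in very ill patients, which the onset time and last-protocol fields help to interpret.

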**Methods and analysis::**

It is a study protocol for a randomized cross-over design in an intensive care unit of a tertiary University hospital. Thirty-one patients aged 18 to 65 years. The study will be divided in 2 phases: the phase one will be held in the first 72 hours of septic shock and the phase two after 3 days of first assessment. Patients will be randomly selected to the intervention protocol (decubitus position with the limbs raised and NMES) and control protocol (decubitus position with the limbs raised without NMES). After this procedure, the patients will be allocated in group 1 (intervention and control protocol) or group 2 (control and intervention protocol) with a wash-out period of 4 to 6 hours between them. The main outcome is mobilization of EPCs. The secondary outcome is metabolic and hemodynamic data. A linear mixed model will be used for analysis of dependent variables and estimated values of the mean of the differences of each effect.

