## Introduction

1

Septic shock is a potentially fatal organ dysfunction caused by an imbalance of the host response to infection. The incidence of septic shock is 18.6 cases per 1000 hospital admissions with a mortality rate of 50.7% in the United States of America.^[1]^ According to international guidelines, patients with septic shock can be identified with clinical signs of sepsis and persistent hypotension requiring a vasopressor to maintain mean arterial pressure ≥ 65 mm Hg and serum lactate levels >2 mmol/L (18 mg/dL) despite adequate fluid resuscitation.^[2–4]^

Changes occur during sepsis in microcirculation, and consequently, there is a decreased blood supply resulting in organ dysfunction. This fact can be explained by the alterations in endothelial barrier function during disease.^[5]^ Indeed, the endothelium is responsible for the interface between tissues and the blood compartment and participates in the local regulation of blood flow and vascular caliber.^[6]^ Studies on the endothelial function and endothelial progenitor cells (EPCs) have been carried out in different groups of patients with metabolic syndrome, cardiovascular disease, in hemodialysis patients as well as in healthy individuals.^[7–9]^ The EPCs are a specific subtype of hematopoietic stem cells that can migrate from the bone marrow into the peripheral circulation. These cells are a potential recovery index of endothelial function and play an important role in neovascularization, repair, and restoration of the endothelium.^[8]^

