Combining the pathophysiology of septic shock, the role of EPCs, the effects of NMES, and the divergence of results of the studies using NMES in patients in septic shock, we hypothesized that NMES initiated an early phase of septic shock and could contribute favorably to the mobilization of EPCs without causing metabolic and hemodynamic impairments. Therefore, the objective of this study is to investigate the effects of NMES in patients with septic shock.

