### Procedures

2.5

The study will be divided into 2 phases, the phase one will be held in the first 72 hours of septic shock; the phase two will be 3 days after the first assessment. Patients will be submitted in a random order to the intervention protocol (decubitus position with the limbs raised and NMES) and control (decubitus position with the limbs raised without NMES). The patients may be allocated in Group 1 (intervention and control) or group 2 (control and intervention) with a wash-out period of 4 to 6 hours between them as visualized in Fig. 1.

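### The adverse event definition leaves out the vasopressor criterion that stops NMES, and vasopressor dose is not a named outcome, so some hemodynamic support given during a session goes uncounted

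*Protocol article*

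**What the plan says.** The Introduction describes septic shock as "persistent hypotension requiring a vasopressor to maintain mean arterial pressure" at 65 mm Hg or more, and its hypothesis is that NMES mobilizes EPCs "without causing metabolic and hemodynamic impairments". The Discussion repeats the safety aim. The abstract states: "The secondary outcome is metabolic and hemodynamic data". The body places the hemodynamic variables under Other outcomes (section 2.8).

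On entry, section 2.2 says: "They should have stable hemodynamic through fluid resuscitation, vasoactive drugs, and mechanical ventilation". The same section has a stopping list, introduced by "Contraindications to begin or continue NMES procedure will include the following", which contains "use of vasopressor >50% of the maximum dose" with limits for dopamine, vasopressin and norepinephrine.

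Section 2.8.4 fixes the event definition. It begins "Adverse event will be defined as any change in mean arterial blood pressure less than 65 mm Hg" and continues with heart rate, arrhythmia, ischemia, oxygen saturation and pain. Any event interrupts the session and is reported. Section 2.8.1 names heart rate, blood pressure, oxygen saturation and breathing frequency as the hemodynamic and respiratory variables, in a list that is worded as open. Section 2.8.5 measures effects from the first to the second value of each protocol.

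**The concern.** In patients whose pressure is supported by a titrated drug, pressure and dose have to be read together. An adverse response to a session can show as a higher dose at an unchanged pressure. The protocol recognizes this when it decides whether NMES may start or go on, because dose is in the stopping list. It then drops dose when it decides what counts as an event and what is named as an outcome.

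The safety half of the hypothesis is at stake. Section 2.8.4 also dispenses with a data-monitoring committee, so the safety conclusion leans heavily on these event and outcome rules. Followed as written, they can give a clean event table and a flat pressure comparison for sessions in which pressure was maintained by giving more vasopressor.

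**Working it through.** The plan gives no figure on this point, so the check sets its rules side by side and follows cases through them.

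**Step 1: the two lists.**

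| Item | Stops NMES (2.2) | Adverse event (2.8.4) |
|---|---|---|
| Mean pressure below 65 mm Hg | yes | yes |
| Vasopressor above 50% of maximum | yes | **no** |
| Heart rate below 50 or above 140 bpm | yes | yes |
| Arrhythmia | yes | yes |
| Ischemia | yes | yes |
| Oxygen saturation | yes | yes |
| Temperature | yes | no |
| Intracranial pressure | yes | no |
| Pain during NMES | not in this list | yes |

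Five of the eight stopping items reappear as events. Of the circulatory ones (pressure, vasopressor, heart rate, arrhythmia, ischemia), vasopressor is the only one dropped. Dose appears in 0 of the 5 physiological event items and in 0 of the 4 variables named in section 2.8.1.

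**Step 2: the range below the ceiling.** The limits in section 2.2 are half the maximum, so the implied maxima are:
- norepinephrine: 1 / 0.5 = 2 μg/kg per minute
- vasopressin: 0.02 / 0.5 = 0.04 U/min
- dopamine: 12.5 / 0.5 = 25 μg/kg per minute

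A rise that stays within the lower half of the range triggers nothing by itself.

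**Step 3: four cases, with no other listed criterion met.**
- *Pressure falls below 65 and the dose is then raised.* The fall is an event and the session is interrupted. This case is covered.
- *The dose is raised while pressure is at or above 65 and stays under the ceiling.* There is no stop and no event. As an illustration, norepinephrine going from 0.2 to 0.8 μg/kg per minute is a fourfold rise (0.8 / 0.2 = 4) and breaches nothing in section 2.2 or 2.8.4. The first-to-second change in pressure may be small.
- *The dose crosses the ceiling during NMES with pressure at or above 65.* Section 2.2 stops the session, but section 2.8.4 counts no event.
- *The same crossing in a control session.* The section 2.2 rule is worded for NMES, so as written there is neither a stop nor an event.

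The last three cases are the gap.

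**Step 4: what a clean event table would show.** Assume all 31 patients complete one phase-one NMES session and no event is counted. The one-sided 95% upper limit for the event rate is 1 − 0.05^(1/31) = 0.092, or 9.2%. That limit covers the listed events only and says nothing about dose escalation.

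**The case against.** The strongest reply is that the event threshold and the treatment target are both 65 mm Hg. If staff titrate to 65, the fall that prompts more drug is itself an event, with no minimum duration required. The uncounted increase needs staff to act while pressure is still at or above 65, in anticipation or toward a higher individual target, and the article describes neither. This stands and limits the point. A reader might infer that every dose increase during a session escapes the count; the text does not support that. The reply does not reach the session stopped for crossing the ceiling, which is a mismatch between two stated rules whatever the titration practice.

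A second reply is that dose is already watched, because section 2.2 applies during NMES. A reader might infer that the protocol has no vasopressor safeguard, and that would be wrong. What is missing is the counting and reporting, and any equivalent rule for control sessions.

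A third is that an article condenses the full protocol, which may well record dose, and that the list in section 2.8.1 is open. This weakens the outcome half of the point. It does not repair the event definition, which the article states in full.

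Finally, heart rate, oxygen saturation, breathing frequency and the calorimetry data could also register harm, and no effect on results has been shown. Both are fair. The point is that the rules can miss such sessions, not that they will.

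**Conclusion.** The point holds in limited form. The event definition omits the vasopressor criterion that the protocol itself uses to stop NMES, and dose is not a named outcome. What goes uncounted is (a) crossing the dose ceiling and (b) increases made while mean pressure is at or above 65 mm Hg. A statement of no hemodynamic impairment would to that extent rest on pressure that may be drug-supported.

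The frequency is unknown and cannot be derived from the article. Stable entry, 30-minute sessions and the event at a pressure below 65 all narrow the gap. A reader might go further and infer that the trial will wrongly declare NMES safe, or that its main result is in doubt. Neither follows: nothing shows how often dose rises in a session, and the EPC primary outcome does not depend on these rules. The conclusion assumes that vasopressors may be adjusted during sessions and that the full protocol has no wider event definition. The change should be made, but it is not critical to the trial.

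**What to change.** 1. Record vasopressor dose at the start and end of every NMES and control session, and add its change to the section 2.8.1 outcomes.
2. Report by protocol the number of sessions with any dose increase and the size of the change, as a paired within-patient comparison or descriptively. Use one combined dose measure or the main agent. A separate linear mixed model per agent would fit poorly, because many 30-minute changes may be exactly zero and not every patient receives each agent.
3. Add crossing of the section 2.2 vasopressor limit to the event list in section 2.8.4.
4. Record increases below that limit as an outcome, without interrupting the session and without labelling each one an adverse event.

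No new start rule for control sessions is needed. Deferring a session could upset the design "with a wash-out period of 4 to 6 hours between them".

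The cost is some wording and a few data fields. Phase one has 31 × 2 = 62 sessions, and two readings each make 124 for a single dose measure. If phase two repeats both sessions (an assumption, as the design figure is not shown), this becomes 124 sessions and 248 readings. Dose must already be checked for NMES, and if the full protocol records it in both sessions, only the definitions change. Some increases will be unrelated to the session, which the control session helps to separate, and the safety summary may look less favourable.
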